*PHQ-2* Patient Health Questionnaire 2, *HADS* Hospital Anxiety and Depression Scale, *PHQ-9* Patient Health Questionnaire 9, *CES-D* Center of Epidemiologic Studies Depression Scale, *BADS* Behavioral Activation for Depression Scale, *ERQ* Emotion Regulation Questionnaire, *CERQ* Cognitive Emotion Regulation Questionnaire, *CCI* Crandell Cognitions Inventory, *BERQ* Behavioral Emotion Regulation Questionnaire, *GAD-7* Generalized Anxiety Disorder 7, *PHQ-4* Patient Health Questionnaire 4

^1^Not sent to participants in the control group

As potential moderators of treatment outcome demographic variables (sex, age, education, and nationality), clinical and psychological characteristics (severity of depressive symptoms at baseline, anxiety symptoms at baseline, coping self-efficacy, physical health, HIV status, motivation, and alcohol and drug use) will be tested at first. Previous research indicated that some of these moderators (e.g., sex and baseline depression severity) might be important in online CBT for depression [34, 35]. In addition, other possible moderators will be investigated exploratory.

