### Statistical analyses

A two-tailed alpha of .05 will be used for significance testing. All analyses will be based on an intention-to-treat (ITT) analysis, which includes all participants who were randomized to one of the groups at the beginning of the study [47]. Baseline differences between conditions will be investigated with chi-square tests for categorical variables and ANOVAs for continuous variables.

To examine the effect of condition on the depressive symptoms at the post-tests, longitudinal multilevel regression analysis (LMRA) will be conducted [48]. A two-level model will be studied: time at level 1 and participants at level 2. The variable time will have four categories indicating the four time points (T0–T4). The baseline (T0) will be used as reference category. The independent variable is condition, the dependent variable is the score on the PHQ-9 or the CES-D, and several covariates will be included in the model (e.g., sex and age). Multiple imputation for missing data is not necessary in LMRA because it can include participants with missing data on one or more time points [48]. The existence of an effect of HIV treatment center will be investigated exploratory.

Furthermore, Cohen’s d will be calculated to indicate within- and between-group effect sizes [49]. In addition, clinically important differences for individual change in depressive symptoms will be examined. Change scores of 5 or more from the pretest to the post-tests will be considered as clinical important differences for the PHQ-9 [50].

With regard to all secondary outcomes, we will study the pre-treatment versus post-treatment changes by using the analyses described above for the PHQ-9 and the CES-D. To examine moderators of the treatment outcome, LMRA will be conducted. Potential moderators will be entered individually. Interaction effects will be investigated (e.g., time x condition x moderator). A limited number of cross-product interactions will be examined, and we will correct for multiple testing. Furthermore, the QUINT (Qualitative Interaction Trees [51]) method will be used to identify subgroups for which the intervention is most effective, by exploratory investigation of the multiple moderators.

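### When baseline depressive severity is the T0 score of the outcome scale, the moderator model has that score on both sides, which miscalibrates the per-visit standard error; post-tests alone should be modelled for this moderator.

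*Protocol article*

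**What the plan says.** Under Assessments, the protocol article names the moderators to be tested first. They include "clinical and psychological characteristics (severity of depressive symptoms at baseline, anxiety symptoms at baseline, coping self-efficacy". The next sentence gives sex and baseline severity as its examples of moderators that earlier research suggests may matter. The article does not say which instrument, or which coding, defines severity.

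Under Statistical analyses, the main model is described as follows: "A two-level model will be studied: time at level 1 and participants at level 2"; "the dependent variable is the score on the PHQ-9 or the CES-D"; "The variable time will have four categories indicating the four time points (T0–T4"), which I read as T0 to T3; and "The baseline (T0) will be used as reference category". T0 is therefore one of the outcome rows.

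The same section carries this model over to moderators: "To examine moderators of the treatment outcome, LMRA will be conducted". Moderators are entered one at a time, and "Interaction effects will be investigated (e.g., time x condition x moderator"). Testing is two-sided at .05, with a correction for multiple testing in the moderator analyses. No exception is made for baseline severity.

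Table 1 shows PHQ-9 and CES-D as the depression scales taken at T0. Its footnote shows that the control group has no T3.

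**The concern.** On the plain reading, baseline severity is the T0 score on PHQ-9 or CES-D. When the outcome is the same scale, that score is both a predictor and the T0 value of the dependent variable. The model reproduces the T0 row perfectly, so every participant has a T0 residual of zero. A model with one residual variance for all occasions averages these zeros with the real post-test residuals. The resulting standard error does not describe the quantity tested, which is how the post-test score depends on condition and T0 score together.

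At stake is the calibration of one moderator test. It answers a stated study question (for whom the program works best) and concerns a moderator that the article picks out by name. A planned multiplicity correction also presupposes valid p-values.

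**Working it through.** **Inputs.** From the article: T0 is an outcome row, time is categorical with four points, the model has two levels, the three-way term is the moderator test, alpha is .05 two-sided, and at least 200 participants are targeted (100 per arm used here). Assumed, because not stated: a random intercept with one residual variance, severity equal to the T0 score of the outcome scale, and the within-person correlations.

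**Plan's own figure.** The article gives none for this test. Its main sample size reproduces (63.77, so 64 per group, for an effect of 0.50 at 80% power) and has no bearing on this point.

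**Step 1: the T0 row.** With T0 score as moderator, the fitted T0 slope is exactly 1 and condition by moderator at T0 is exactly 0. All T0 residuals vanish.

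**Step 2: effect on the standard error.** Let v be the post-test residual variance given T0, and r the correlation between post-test residuals given T0.
- Four time points: the expected within-person mean square is (1/3)[3v − (3v + 6rv)/4] = v(0.75 − 0.5r). The model takes the T1-versus-T0 contrast to have twice this variance, v(1.5 − r). The true value is v, because T0 contributes nothing. The variance ratio is 1.5 − r.
- Three time points: the same steps give 4/3 − 2r/3.
- Both ratios equal 1 only if r = 0.5.

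**Step 3: when compound symmetry holds.** With common correlation ρ, r = (ρ − ρ²)/(1 − ρ²) = ρ/(1 + ρ), which is below 0.5 for every ρ below 1. The standard error is then always too large. The rejection rate is 2[1 − Φ(1.96 × SE ratio)]. A test with 80% power under a correct standard error keeps Φ(1.96 + 0.84 − 1.96 × SE ratio).

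| ρ | r | variance ratio, 4 points | SE ratio | rejection at nominal 5% | power instead of 80% |
|---|---|---|---|---|---|
| .3 | .231 | 1.269 | 1.127 | 2.7% | 72% |
| .5 | .333 | 1.167 | 1.080 | 3.4% | 75% |
| .7 | .412 | 1.088 | 1.043 | 4.1% | 78% |

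Simulation with 100 per arm, no true moderation and 3,000 trials per setting agrees: 2.5% to 4.2% per visit with four time points, with and without control T3. Across all compound-symmetry runs the range is about 2.5% to 4.9%. The mean of the three-way estimate stayed within 0.006 of zero.

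**Step 4: other correlation patterns.** Here r = (b − a²)/(1 − a²) for baseline-to-post correlation a and post-to-post correlation b. The comparator is a moderator unrelated to the outcome. For it the model variance of the T1−T0 contrast is 2(1 − mean correlation) and the true variance is 2(1 − a). Four time points:
- a = .3, b = .7. T0 score: r = .67, variance ratio 0.83, rejection 7.4%. Unrelated moderator: 2(1 − .5) = 1.0 against 2(1 − .3) = 1.4, ratio 0.71, rejection 9.8%.
- a = .5, b = .8. T0 score: r = .73, variance ratio 0.77, rejection 8.6%. Unrelated moderator: 2(1 − .65) = 0.70 against 1.0, ratio 0.70, rejection 10.1%.

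Simulation agrees. For .3/.7, the T0 score gives 6.4% to 8.1% and the unrelated moderator 8.8% to 10.7%. For .5/.8 the figures are 8.3% to 9.4% and 9.8% to 10.4%.

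**Step 5: joint test over visits.** Over all post-baseline contrasts, rejection for the T0-score moderator was 4.4% to 6.2%. In the layout without control T3, the joint T1 and T2 test gave 4.4% to 5.7% under compound symmetry and 5.5% to 7.1% under the other patterns.

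**Step 6: T0 removed from the outcome.** Regressing T1 on condition, T0 score and their product gave 4.5% to 5.5% rejection and SE ratios of 0.97 to 1.02 in every setting with the T0 score as moderator.

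**Step 7: the lower-order term.** The time by severity slope without treatment is (correlation × post SD / baseline SD) − 1. With assumed SDs of 4.3 and 5.2 and correlation .45, it is .45 × 5.2/4.3 − 1 = −0.46. Five more points at T0 then go with 5 × 0.46 = 2.3 points more apparent improvement in both arms, through regression to the mean.

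**The case against.** A reader might infer that the self-regression inflates false positives to 8% or 9%. It does not. In the settings with that inflation, an unrelated moderator on the same data does as badly or worse (Step 4). The cause there is a compound-symmetry model fitted to data without compound symmetry, which affects every moderator. What belongs to the self-regression is the conservatism in Step 3. That objection stands in full.

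It also stands that the joint test is near nominal, so the fault lies mainly in the per-visit contrasts.

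The premises are partly open. No instrument is named. PHQ-9 is also taken at the researchers' screening, and CES-D is a second scale. A different score correlating .8 with T0 gave 4.6% to 5.1%, so such a choice would avoid the problem. The covariance structure is not stated and may properly sit in an analysis plan. This limits the point without removing it: the article equates baseline with T0 and makes no exception. An unstructured covariance would not rescue the model either, because the T0 residual variance would be zero and the matrix singular.

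A reader might also infer that the article will present the time by severity term as treatment response. Nothing in it says so. Its example of a moderator test contains condition.

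**Conclusion.** The point holds in a limited form. For same-instrument pairs, the T0 score stands on both sides of the moderator model, and the per-visit standard error of the three-way term is miscalibrated. The estimate is unbiased.

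Under a random-intercept model and true compound symmetry, with four time points and correlations of .3 to .7, the standard error is about 4% to 13% too large. The cost is power: a test that should have 80% would have about 72% to 78%. The documents do not support a claim that this overlap creates false moderators.

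The conclusion rests on three assumptions: severity is the T0 score of the outcome scale, there is one residual variance, and the correlations lie in the range shown. It concerns one moderator in a secondary analysis. The primary effect is not affected.

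**What to change.** For baseline severity with the same instrument as outcome, take T0 out of the dependent variable. Model only the post-tests that both arms have, T1 and T2, on T0 score, condition, time and their interactions, and test condition by T0 score. Name the instrument that defines severity. State that moderation is read only from terms containing condition, because time by severity reflects regression to the mean.

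The cost is a different data layout for one moderator. It needs no new data and loses no information for this test, because the T0 row carries none.

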**Methods/design:**

The effectiveness of the program will be investigated by comparing the intervention group with a waiting list-control group in a randomized controlled design, by including a pretest and three post-tests. The self-help program contains four main components: activation, relaxation, changing maladaptive cognitions, and goal attainment. Participants with mild to moderate depressive symptoms will work on the program for 6 to 10 weeks, during which a coach will provide motivational support by telephone once a week. Participants in the control condition will receive weekly minimal support from a coach for 8 weeks, and after the second post-test, they can gain access to the self-help program. Depressive symptoms and possible mediators (e.g., activation, cognitive coping, self-efficacy, and goal adjustment) will be assessed by self-report three times during the intervention/waiting period and at the pretest and first post-test.

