### Study conditions

#### Online self-help intervention

The self-help intervention is grounded in the theories of self-regulation and stress-coping, incorporating techniques of CBT and stress-management. The content of the program reflects four main components covered in eight lessons: activation, relaxation, changing maladaptive cognitions, and goal attainment. The program contains a combination of psycho-education, exercises, and assignments, all strengthened by motivation and support to increase the effectiveness and to minimize the attrition over time.

The intervention is offered through a secured website that contains the complete work program. Participants work on the intervention 1-2 hours a week for a period of 6-10 weeks. The program starts with an introduction, and participants are asked to think of a small activity to perform (e.g., taking a short walk; lesson 1). They are stimulated to perform this activity in the following weeks and to expand this to other activities. Furthermore, participants will be instructed to do relaxation exercises and to continue these exercises in the coming weeks (lesson 2). Thereafter, participants learn to identify and change irrational cognitions (by challenging negative thoughts) and to evoke a strong and positive feeling when they experience negative feelings (lessons 3-5). Furthermore, participants are guided to formulate a new, realistic, concrete goal (such as quit smoking) and work on the stepwise attainment of this goal (lessons 6-7). Finally, the participant will work on a concluding and summarizing lesson (lesson 8). All participants will receive support from a coach during the intervention (see below).

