The mediator variables and the dependent variable will be measured three times during the intervention/waiting period, at the pretest, and at the first post-test. The following mediator variables will be assessed in the study: activation (two items of the BADS), physical tension (two items), cognitive reappraisal (two items of the ERQ), cognitive coping (12 items of the CERQ), goal adjustment (two items of the Goal Disengagement and Reengagement Scale), symptoms of anxiety (PHQ-4 [36]), and coping self-efficacy (two items). The dependent variable in the mediational analysis is the depressive symptoms (PHQ-4). The questions (regarding, for example, symptoms and cognitions) that will be asked during the intervention/waiting period will refer to the last week. The assessments will be administered three times during the intervention/waiting period because, at these moments, we expect change in the mediating variables. The assessments are linked to the lessons of the self-help program for participants in the intervention group. At the first measurement, we expect a change in the behavioral activation; at the second measurement, we expect a change in the physical tension; at the third measurement, we expect a change in the cognitive reappraisal and cognitive coping; and at the post-test, we expect a change in the goal adjustment. Coping self-efficacy and anxiety are expected to change over the entire course of the treatment.

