#### Patient Health Questionnaire 2 and Patient Health Questionnaire 4 (PHQ-2 and PHQ-4)

The PHQ-4 [36] will be used to assess depressive and anxiety symptoms during the intervention or waiting period (for the mediational analysis). It consists of the first two questions of the PHQ-9 and the first two questions of the GAD-7. Items are rated on a four-point scale ranging from 0 “not at all” to 3 “nearly every day.” Higher scores indicate more pathology. The internal reliability, construct validity, and factorial validity are adequate [36]. The PHQ-2 [24] consists of the first two questions of the PHQ-9 and will be used by the HIV treatment centers to screen for depressive symptoms.

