Mediation will be tested by examining the indirect effect of the independent variable (condition) on the dependent variable (depressive symptoms) through the proposed mediators. Mediation analysis will be conducted by using latent difference score models, which are recommended with repeated measurements and multiple mediators [52]. These models focus on intra-individual change and individual differences in that change.

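### The stated mediation schedule stops at T1, where goal adjustment is expected to change, so that expected change has no later depression measurement and its link with depression cannot be given a direction

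*Protocol article*

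**What the plan says.** The Assessments section sets the mediation occasions: "The mediator variables and the dependent variable will be measured three times during the intervention/waiting period, at the pretest, and at the first post-test". The abstract gives the same five: depressive symptoms and possible mediators "will be assessed by self-report three times during the intervention/waiting period and at the pretest and first post-test". The mediation outcome is depressive symptoms on the PHQ-4.

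The same section ties mediators to occasions. Activation is expected to move at the first in-treatment assessment and physical tension at the second. Then "at the third measurement, we expect a change in the cognitive reappraisal and cognitive coping", and finally "at the post-test, we expect a change in the goal adjustment". Anxiety and coping self-efficacy are expected to change throughout. This order follows the program: goal work is in lessons 6 and 7, after the cognitive lessons 3 to 5, and only a summary lesson follows.

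Under Statistical analyses, "Mediation analysis will be conducted by using latent difference score models". That paragraph names no final outcome occasion and does not mention T2.

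Table 1 schedules both the goal scale and the PHQ-9 at T2. The Procedure section has controls receive the program only after T2, about 5 months after T0. T3 is not sent to controls.

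**The concern.** A claim that a mediator carries a treatment effect needs the mediator to move before the outcome does. The staggered schedule achieves this for activation, tension, and reappraisal and coping. It does not for goal adjustment, whose expected change is first seen at the occasion that also closes the outcome series.

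The article presents knowledge of the mechanisms as a strength and intends to use it to adapt the program. Goal attainment is one of the four components. If the program lifts mood by another route and people who are less depressed then find it easier to adjust goals, a model ending at T1 can still report an indirect effect through goal adjustment. That result could be used to keep or expand the goal lessons when the evidence does not show which came first.

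**Working it through.** **1. The plan's own figure.** The article gives no figure for the mediation analysis. Its sample size serves the primary outcome. For d = 0.50, two-sided alpha .05 and power .80, a two-sample t-test needs 63.8, so 64 per group, as stated (power at 64 is 0.801). With 15 % dropout, 128 / 0.85 = 150.6, against 150 stated. This does not bear on temporal order. It only supplies two sizes for the illustration below: 128 completers and the recruitment target of 200.

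**2. Outcome points after each expected change.** Call the in-treatment assessments M1, M2 and M3. The stated mediation series is T0, M1, M2, M3, T1.

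| Mediator | Expected change seen at | Later outcome points in the series |
|---|---|---|
| Activation | M1 | 3 (M2, M3, T1) |
| Physical tension | M2 | 2 (M3, T1) |
| Reappraisal, cognitive coping | M3 | 1 (T1) |
| Goal adjustment | T1 | 0 |

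A lagged path from goal adjustment at M3 to depression change from M3 to T1 can be estimated, but it uses goal adjustment before its expected change.

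**3. Why the M3-to-T1 association has no direction.** Write x for condition, m for goal adjustment at T1, y for depression at T1, and condition on the M3 values. The joint distribution factors both ways:

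p(m | x) p(y | m, x) = p(y | x) p(m | y, x)

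Both orderings therefore reach the same likelihood. This holds for any path sizes.

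**4. Illustration.** The path values are assumptions, and ordinary regressions stand in for the latent difference score model. Residual SDs at T1 and T2 are 0.8 (variance 0.64), there are 1,000 simulated trials per setting at N = 128 and 200, and significance means that both paths exceed 1.96 standard errors.

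- *Reverse only:* condition lowers T1 depression by 0.5, and lower depression raises goal adjustment (coefficient -0.4). The T1 model then estimates a = (-0.5)(-0.4) = 0.20 and b = (-0.4 × 0.64) / (0.64 + 0.16 × 0.64) = -0.256 / 0.7424 = -0.345. The apparent indirect effect is 0.20 × (-0.345) = -0.069, although none exists.
- *Forward:* condition raises goal adjustment by 0.5, which lowers T1 depression (-0.4) and, given T1 depression, T2 depression (-0.25). The expected indirect effects are 0.5 × (-0.4) = -0.20 at T1 and 0.5 × (-0.25) = -0.125 on the lagged path.

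| Truth | N | T1 model: indirect effect (significant) | T2 path, adjusted for T1 depression (significant) |
|---|---|---|---|
| Reverse only | 128 | -0.070 (25.5 %) | 0.000 (1.8 %) |
| Reverse only | 200 | -0.067 (36.9 %) | 0.000 (1.9 %) |
| Forward | 128 | -0.195 (92.7 %) | -0.121 (67.1 %) |
| Forward | 200 | -0.199 (99.6 %) | -0.123 (89.6 %) |

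The log-likelihoods of the two orderings differed only by rounding, even at N = 100,000.

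**5. What T2 cannot do.** If the forward effect is complete by T1, replace -0.25 by 0. The lagged path becomes 0.5 × 0 = 0, while the true mediated effect at T1 is still -0.20. The 67.1 % and 89.6 % thus depend on an assumed effect that persists.

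**6. Is the T2 outcome available on the same scale?** Of the PHQ-4 the article says "It consists of the first two questions of the PHQ-9 and the first two questions of the GAD-7". Table 1 lists the PHQ-4 only during the intervention/waiting period, so at T0 and T1 its depression items already have to come from the PHQ-9. The PHQ-9 is also given at T2, so change from T1 to T2 can be scored in the same way.

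**The case against.** The strongest reply is that the Assessments text is a measurement schedule, and that the three-sentence mediation paragraph leaves lags and final outcome to a fuller plan that is not shown. This stands in part. A reader might infer that the trial has decided against using T2 for mediation; the article does not say so. It simply does not assign T2 to that analysis. It does, however, name T1 as the last mediation occasion in two places and explains the timing mediator by mediator, so the mismatch lies in stated text.

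A reader might also infer that goal adjustment cannot be tested as a mediator at all, or that one of the four components is unanswerable. The documents do not support that. Goal adjustment is measured at all five occasions, so earlier lagged paths can be estimated in both directions. Its post-test change by condition is a randomised comparison, also analysed as a secondary outcome. Only the direction of the M3-to-T1 link with depression is undetermined.

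Nor is the single later outcome for reappraisal and coping a defect: one is enough for a lagged path.

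Finally, it is tempting to rest the whole goal-adjustment claim on the T2 path. That goes too far. An effect complete by T1 would be missed, and the T1-to-T2 interval also contains attrition, continued use of the program and possible outside treatment.

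**Conclusion.** The point holds for the change that the protocol itself expects. Within the stated mediation schedule, the change in goal adjustment from the third in-treatment assessment to T1 has no later depression measurement, and its association with depression change over that interval cannot be read as mechanism rather than consequence. The count of 0 later outcomes, against 3, 2 and 1 for the other lesson-linked mediators, follows directly from the text, and the equal fit of the two orderings does not depend on assumed values. The simulated percentages do depend on them and only illustrate the risk.

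The reach is limited: one of seven listed mediators, in a secondary question. The primary comparison, sample size and data collection are unaffected. The change is worth making because it costs little and helps the trial answer its own question. If the full analysis plan already carries the mediation model to T2, only the article's description falls short.

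**What to change.** Extend the latent difference score model to T2. Add a lagged path from goal-adjustment change up to T1 to change in depressive symptoms from T1 to T2, scored from the first two PHQ-9 items and adjusted for prior depression. Stop at T2, because controls are not assessed at T3.

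Report this path beside the T1 model, not in place of it. Label the same-interval goal-adjustment result at T1 as exploratory and not temporally ordered.

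The cost is analysis wording only: the PHQ-9 and the goal scale are already scheduled at T2 in both arms, before controls receive the program. Three downsides should be stated with the result. Some participants will be lost between T1 and T2. An effect already complete by T1 may not appear on the lagged path, so a null there does not rule out mediation. A later outcome gives temporal order but does not remove unmeasured confounding between mediator and outcome.
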